## Abstract

**Background:** Despite strong guideline recommendations, participation in cardiac rehabilitation (CR) among patients with chronic heart failure (CHF) remains low due to logistical, geographical, and psychosocial barriers. Telerehabilitation may help overcome these limitations by offering remote, structured exercise programs supported by digital technologies. **Objective:** The TELEREHAB-HF study aims to evaluate the efficacy of an 8-week, home-based cardiac telerehabilitation program compared to standard in-person rehabilitation in patients with CHF. **Methods:** This is a prospective, controlled cohort study involving 220 adult patients with CHF (NYHA class I–III) clinically stable and on optimized therapy. Participants are assigned to either a telerehabilitation group (remote CR via a digital platform with wearable sensors and real-time physiotherapist supervision) or a standard in-person rehabilitation group. The primary outcome is the change in peak oxygen uptake (VO_2_max) at 8 weeks. Secondary outcomes include quality of life, functional performance, biochemical and echocardiographic parameters, and cognitive function, assessed at baseline and at 4, 8, 16, and 24 weeks. **Expected Results**: We hypothesize that telerehabilitation will be non-inferior to standard CR in improving functional capacity and secondary outcomes, with additional benefits in accessibility and adherence. Data from remote monitoring may also support a translational “rehabilomics” approach to exploring exercise-induced biomarker changes. **Conclusions:** This study seeks to assess the clinical effectiveness, safety, and feasibility of a home-based telerehabilitation model for CHF, with the goal of informing future strategies for broader implementation and personalized rehabilitation. Trial Registration: ClinicalTrials.gov Identifier: NCT07023536

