### 9.2. Secondary Endpoint Analysis

Continuous variables will be presented as mean ± standard deviation for normally distributed variables, and as median and interquartile range for those with non-normal distribution. Categorical data will be expressed as absolute numbers and percentages. The Shapiro–Wilk test will be used to assess normality.

For repeated measurements (e.g., QoL scores, biochemical markers, functional parameters), comparisons across timepoints (T0, T1, T2, T3, T4) will be conducted using one-way repeated measures ANOVA for normally distributed data, or Friedman test for non-parametric data.For post hoc comparisons, Bonferroni correction will be applied to control for type I error.Categorical variables (e.g., proportion of patients with adverse events) will be compared using the Pearson chi-square test or Fisher’s exact test where appropriate.

A two-sided *p*-value < 0.05 will be considered statistically significant for all final analyses.

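### The tests named for repeated secondary outcomes have no arm or arm-by-time term, so they cannot address the stated between-arm hypothesis

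*Protocol article*

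**What the plan says.** Section 9.2 of the protocol article fixes the method for repeatedly measured secondary outcomes, giving quality of life, biochemical and functional measures as examples. Values at T0 to T4 are to be compared by "one-way repeated measures ANOVA for normally distributed data, or Friedman test for non-parametric data". The next sentence adds: "For post hoc comparisons, Bonferroni correction will be applied to control for type I error". No arm contrast is named. Echocardiography and MMSE are not among the examples, but they are measured repeatedly (section 8, Table 3) and no other method is given for them.

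The Abstract states the hypothesis that "telerehabilitation will be non-inferior to standard CR in improving functional capacity and secondary outcomes".

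Rehabilitation type appears as a predictor in one place only, the logistic regression for the primary responder endpoint (section 9.1). Categorical variables such as adverse events have their own tests, Pearson chi-square or Fisher (section 9.2). Allocation follows patient preference and logistics. Section 2 promises statistical adjustment, with propensity scores as an example, but ties it to no secondary analysis.

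**The concern.** A one-way repeated-measures analysis asks whether an outcome changes over time. The Abstract asks whether one mode of delivery is as good as the other. If section 9.2 is followed as written, KCCQ-12, SF-36, 6MWT, SPPB, the biomarkers and, by extension, echocardiography and MMSE would yield only statements that patients changed.

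The risk lies in how such results are read. Both groups receive an active exercise programme, so improvement in both is the likely finding. It would be easy to present that as comparability, which is the conclusion hypothesised. The opposite error is also available: inferring a difference because one arm reaches significance and the other does not. Because patients choose their arm, any between-arm statement also needs an adjusted estimate, and these tests contain no arm contrast to which an adjustment could apply.

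**Working it through.** The plan gives no figure to reproduce here. The point is structural, and a simulation shows what it means in practice.

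**Step 1: terms in the named tests.** The one-way repeated-measures model is y_ij = μ + subject_i + time_j + e_ij for patient i at visit j. Friedman's test ranks each patient's own values across visits. Neither has a group term or a group-by-time term. Pooled over two equal arms, the time effect at visit j is the average of the two arm means, (m_0j + m_1j)/2, and any divergence between arms goes into the residual.

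**Step 2: what the pooled test sees.** Take changes from baseline in total-SD units, reached by T2 and held to T4.
- Equal gains: (0.50 + 0.50)/2 = 0.50. The arm difference is 0.
- Opposite movement: (0.25 − 0.25)/2 = 0. The arm difference is 0.50.
- Telerehabilitation gains half: (0.50 + 0.25)/2 = 0.375. The arm difference is 0.25.

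The pooled effect is largest where the arms do not differ and zero where they differ most.

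**Step 3: simulation.** Inputs: 200 patients (the pre-dropout number in section 9.3) and alpha 0.05 two-sided (section 9.2). Assumed, not in the documents: an even split of 100 per arm, five visits, between-patient SD 0.8 and residual SD 0.6 (total √(0.64 + 0.36) = 1.0), complete data, 2,000 runs. Rejection rates:

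| Scenario | Pooled one-way ANOVA | Pooled Friedman | One-way ANOVA significant in both arms separately | Group-by-time F test |
|---|---|---|---|---|
| Equal gains | 100% | 100% | 100% | 4.8% |
| Opposite movement | 3.8% | 5.0% | 76% | 99.7% |
| Telerehabilitation gains half | 100% | 99.95% | 85% | 53% |
| No change in either arm | 5.4% | 5.5% | 0.3% | 4.9% |

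The Monte Carlo standard error near 5% is √(0.05 × 0.95/2000) = 0.5 percentage points.

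**Step 4: reading.** The pooled tests follow the average change and say nothing about the arm difference. Running the ANOVA separately by arm does not repair this: significance in both arms occurs in 100% of runs when the arms are equal and in 85% when one gains half as much, so it barely separates the two situations. Only the group-by-time test responds to the arm difference. A non-significant group-by-time test would still not establish non-inferiority. That needs a margin and a confidence interval for the difference.

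**The case against.** The strongest reply is that these are secondary outcomes and that the non-inferiority wording for them is one clause in the Abstract. The body is softer: section 1 lists secondary measures without a hypothesis, section 8 speaks of a longitudinal evaluation of both programmes, and section 10 expects favourable trends. A within-arm analysis over time partly serves those aims, and the primary endpoint has a between-arm model. This stands as an argument about severity. It does not remove the mismatch, because section 11 also contemplates judging whether telerehabilitation is as good as standard care or better.

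A second reply is that an article leaves detail to the analysis plan. That would hold if the article were silent. Instead it names the tests, and an analysis plan that follows it inherits the problem.

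Two stronger readings are tempting, and the documents do not support them.
- A reader might infer that every patient with a missed visit would be dropped, and more often in one arm. The article does not say how incomplete visits are handled, which is commonly left to the analysis plan, and it gives no missed-visit rate per visit or per arm. It also offers telerehabilitation patients a move to in-person sessions (sections 5 and 7).
- A reader might infer that confounding cannot be addressed at all. Section 2 promises propensity-score methods and section 12 mentions matching, which acts on the sample before any test. The supportable point is narrower: the named tests contain no arm contrast to adjust.

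**Conclusion.** The point holds for the repeated secondary outcomes: quality of life, functional and biochemical measures and, because no other method is given, echocardiography and MMSE. The prescribed tests cannot address the Abstract's between-arm hypothesis at any sample size. That conclusion follows from the form of the tests and needs no numerical assumption. The simulated rates illustrate it and depend on the assumed SDs, effect pattern and even split.

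It does not extend to adverse events, for which chi-square or Fisher tests are named, or to the primary logistic regression. Since the primary endpoint has its own between-arm model, this should be fixed but does not put the main conclusion at risk.

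**What to change.** For each repeated secondary outcome, make a between-arm comparison the main analysis:
- **Model.** For example, a mixed model on all available post-baseline visits with group, visit, group-by-visit and the baseline value as covariate. Baseline-adjusted ANCOVA at T2 and T4 would also supply the missing contrast.
- **Confounding.** Apply the propensity-score adjustment already promised in section 2, with the confounders fixed in advance. Section 9.1 picks covariates from baseline comparisons, so it offers no prespecified set to reuse.
- **Reporting.** Give the adjusted arm difference with its confidence interval at T2 and T4. Keep within-arm change as description.
- **Scale.** Log-transform skewed biomarkers such as BNP and NT-proBNP. For bounded scores such as SPPB (0–12) and MMSE (0–30), use a rank-based or ordinal between-arm method if needed.
- **Hypothesis.** Either state a margin for every secondary outcome to be claimed as non-inferior, or reword the secondary hypothesis as estimation of the arm difference.

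The cost is revised wording and slightly more analysis work, with no new data or visits. Data collection is described as ongoing, so the change can be made before results are seen. It does not guarantee precision: in the half-gain scenario the group-by-time test rejected in only 53% of runs.

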## 9. Statistical Analysis

### 9.1. Primary Endpoint Analysis

To evaluate the primary endpoint of the study—defined as a ≥10% improvement in VO_2_max at 8 weeks—paired comparisons between baseline and post-intervention values will be performed using a paired t-test for normally distributed data [36,37,38]. For non-normally distributed data, the Wilcoxon Signed-Rank test will be applied. Additionally, the proportion of patients achieving the predefined VO_2_max improvement threshold will be analyzed using logistic regression, with “Rehabilitation Type (Telerehabilitation vs. Standard)” as the main predictor. The model will be adjusted for clinically relevant covariates identified through baseline comparisons using ANOVA or chi-square tests. Odds ratios and 90% confidence intervals will be reported.

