### 9.3. Sample Size Calculation

Based on the primary endpoint, the required sample size was calculated using G*Power software (Version 3.1.9.7). Assuming a 10% increase in VO_2_max in the intervention group compared to the control group, with a two-sided alpha level of 0.05 and statistical power (1–β) of 90%, the estimated sample size is 200 patients.

To compensate for a potential 10% dropout rate, the final target enrollment is 220 patients with CHF. This sample size is considered sufficient to detect clinically relevant differences in functional capacity and allows for robust evaluation of secondary outcomes including QoL, echocardiographic and biochemical parameters.

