## 10. Expected Results

We expect to observe that the telerehabilitation group will demonstrate a significant improvement in functional capacity, as evidenced by a ≥10% increase in VO_2_max after 8 weeks of intervention, compared to the standard in-person rehabilitation group. This improvement is expected to be sustained at 24 weeks, indicating the long-term efficacy of the program. Furthermore, we expect to observe positive trends in secondary outcomes, including enhanced QoL (as measured by KCCQ-12 and SF-36), improved functional performance (6MWT, SPPB), and favorable changes in biochemical markers (BNP, NT-proBNP, creatinine, and electrolytes).

In the telerehabilitation group, the use of real-time monitoring and personalized feedback is also expected to improve adherence and safety, with a low incidence of adverse events. Additionally, we anticipate that echocardiographic parameters, such as LVEF and diastolic function indices (E/A, E/e’), will show measurable improvement or stabilization.

Overall, the study is expected to demonstrate that a structured, telerehabilitation program is not only clinically effective and safe, but also a feasible and scalable alternative to traditional CR for patients with CHF.

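### The only between-arm safety analysis stated is a chi-square/Fisher difference test at p<0.05, which cannot support a claim of comparable safety

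*Protocol article*

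**What the plan says.** Safety is an aim of the study (Abstract and section 11) and an expected conclusion. Section 10 says that "the study is expected to demonstrate that a structured, telerehabilitation program is not only clinically effective and safe". The Abstract adds a comparative hypothesis: "We hypothesize that telerehabilitation will be non-inferior to standard CR in improving functional capacity and secondary outcomes". Section 8 and Table 3 list adverse events as a secondary outcome.

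The between-arm analysis of adverse events is given in one sentence of section 9.2: "Categorical variables (e.g., proportion of patients with adverse events) will be compared using the Pearson chi-square test or Fisher’s exact test where appropriate". The decision rule follows in the same section: "A two-sided *p*-value < 0.05 will be considered statistically significant for all final analyses". Section 9.2 also says that categorical data will be shown as counts and percentages.

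The one mention of confidence intervals is in section 9.1, for the primary endpoint: "Odds ratios and 90% confidence intervals will be reported". No interval, margin or acceptable rate is attached to adverse events.

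On size, section 9.3 says of the primary endpoint: "with a two-sided alpha level of 0.05 and statistical power (1–β) of 90%, the estimated sample size is 200 patients". It adds that the enrolment of 220 "allows for robust evaluation of secondary outcomes". That sentence goes on to name quality of life, echocardiographic and biochemical measures. Adverse events are not among those named.

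**The concern.** A significance test of a difference can give evidence that two rates differ. It cannot by itself give evidence that one rate is not materially worse than the other. That needs an upper bound on the excess. The protocol pairs a safety conclusion and a non-inferiority hypothesis with a test of the first kind and no bound. The article has chosen and stated this analysis, so the point is a mismatch between method and intended conclusion, not a missing detail.

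At stake is how a real excess of events among patients exercising at home would appear in the results. With about 100 patients per arm and low event rates, a doubling can easily give p>0.05. Without an interval beside the p-value, the reader cannot see how large an excess the data leave open.

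**Working it through.** **Inputs from the protocol article.** 200 evaluable and 220 enrolled patients (section 9.3); two-sided 0.05 and Pearson chi-square or Fisher (section 9.2).

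**Assumptions, because the article gives no figure.** Arm sizes: allocation is by patient preference and logistics (section 2), so 100 per arm is assumed and other splits are tried. Event rate: section 10 says only that a low incidence is expected in the remote arm, so a range of in-person rates is used.

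**The plan's own figure.** There is no power statement for adverse events to reproduce. The 200 belongs to the primary endpoint and cannot be rebuilt without a standard deviation or responder rate; it corresponds to a standardised difference of about 0.46. Enrolment follows as 200 × 1.10 = 220.

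**Step 1: chance of missing a doubling.** By the normal approximation for 5% versus 10%, 100 per arm:
- pooled rate 0.075; standard error under no difference = √(2 × 0.075 × 0.925 / 100) = 0.0372
- standard error under the alternative = √((0.05 × 0.95 + 0.10 × 0.90) / 100) = 0.0371
- power ≈ Φ((0.05 − 1.96 × 0.0372) / 0.0371) = Φ(−0.62) ≈ 0.27, so the miss probability is about 0.73

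Exact enumeration of the two binomials gives these miss probabilities at 100 per arm:

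| In-person vs remote | Chi-square | Fisher |
|---|---|---|
| 2% vs 4% | 89% | 96% |
| 5% vs 10% | 73% | 81% |
| 7.5% vs 15% | 60% | 69% |
| 10% vs 20% | 48% | 56% |
| 15% vs 30% | 27% | 33% |
| 20% vs 40% | 12% | 16% |
| 30% vs 60% | 1% | 1% |

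**Step 2: sensitivity to arm sizes** (chi-square / Fisher):
- 110 per arm, no dropout: 5% vs 10%, 70% / 79%; 10% vs 20%, 44% / 52%
- 133 remote, 67 in-person: 79% / 84%; 56% / 61%
- 67 remote, 133 in-person: 73% / 76%; 50% / 54%

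**Step 3: what an interval would show** (assumed counts, 100 per arm, Newcombe 95% interval for remote minus in-person):
- 5 vs 5 events: the Wilson limits for 5/100 are 0.0215 and 0.1118. The upper limit of the difference is √((0.1118 − 0.05)² + (0.05 − 0.0215)²) = 0.068, or +6.8 points. The log-method risk ratio runs up to 3.3.
- 10 vs 10 events: upper limit +8.7 points, risk ratio up to 2.3.
- 12 remote vs 5 in-person: z = 0.07 / √(0.085 × 0.915 × 2/100) = 1.77, p = 0.08 (Fisher 0.13); interval −0.9 to +15.3 points.
- 0/100 in one arm: exact upper limit 1 − 0.025^(1/100) = 3.6%.

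So at these rates even identical counts do not exclude a doubling.

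**Step 4: the unit.** Section 9.2 tests patients with an event. Table 3 measures events over treatments administered. Section 3 schedules 5 × 4 + 3 × 4 = 32 sessions per patient, so 100 patients have 3,200 planned sessions. Ten events in ten patients are then 10% on one scale and 10/3,200 = 0.3% on the other. The figures above apply only to the patient-level unit.

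**The case against.** The strongest reply is that the protocol nowhere says p>0.05 will be read as safety. A reader might infer that a non-significant p-value is the only possible support for the safety conclusion, or that a doubling would probably be published as no difference. The article does not support either. Sections 10 and 11 link safety to a low observed rate of events, and section 9.2 promises counts and percentages, so 12% versus 5% would be visible. This stands. What remains is that no other between-arm inferential basis is stated.

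A reader might also take a miss rate of 50–80% as a property of the planned size. It is not. It needs an in-person rate of 5–10% and roughly equal arms. Section 8 defines adverse events broadly, including device issues, and Table 3 follows them to 24 weeks, so higher rates are plausible, and there the test does much better. At 10% versus 20% the chi-square test detects the doubling slightly more often than not (power 0.518). The Fisher figures apply only where that test is judged appropriate, which under the usual expected-count rule would be seldom at 5–10%.

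Section 9.3 might be read as claiming robustness for adverse events. It names other outcomes; its wording leaves adverse events open but does not assert them.

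Finally, interval methods are often left to an analysis plan, and a chi-square or Fisher test on an unpowered safety outcome is common. That is fair as to the choice of interval formula. It does not remove the mismatch between the stated test and the stated conclusion.

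**Conclusion.** The point holds in a limited form. The article expects to demonstrate safety and hypothesises non-inferiority on secondary outcomes, but the one between-arm safety analysis it states is a difference test at two-sided p<0.05, which cannot support comparable safety at any sample size. How often that test would overlook real harm is conditional. With 100 patients per arm and 5–10% of in-person patients having an event, a doubling is missed 48–73% of the time by chi-square and 56–81% by Fisher; at 2% versus 4% it is 89% / 96%, and at 20% versus 40% only 12% / 16%. Rates and arm sizes are assumptions, and all figures presume the patient-level unit of section 9.2. No intention to treat non-significance as proof of safety can be attributed to the authors.

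**What to change.** In section 9.2:
- Report the remote-minus-in-person difference in the proportion of patients with adverse events with a two-sided 95% confidence interval (for example Newcombe), and each arm's proportion with an exact 95% interval.
- Where event numbers allow, add an estimate using the propensity adjustment already promised in section 2. Allocation follows patient preference, so the crude difference is open to confounding.
- Show device issues separately from clinical events. Section 8 counts both, while section 4 says the in-person arm uses no remote-monitoring devices, so part of a crude excess would be built in.
- Reconcile the patient-level proportion with the events-per-treatment unit in Table 3.
- State that comparative safety is read from the upper confidence limit, and that a non-significant test is not evidence of safety.

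In section 9.3, clarify that the statement on secondary outcomes does not extend to adverse events, and give the precision instead: with 5/100 in each arm, an excess of up to about 7 percentage points is not excluded. Align the wording of section 10 with this.

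The cost is mainly wording, plus one adjusted analysis, with no added patients or assessments. The downside is a more cautious safety statement.

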## 2. Methods

### Study Design and Population

The TELEREHAB-HF study is a single-center, prospective, observational, non-pharmacological cohort trial designed to evaluate the clinical efficacy of a home-based, supervised cardiac telerehabilitation program in patients with CHF. The trial will be conducted at the tertiary care center Azienda Ospedaliera Universitaria (AOU) “San Giovanni di Dio e Ruggi d’Aragona” in Salerno, Italy, in collaboration with the University of Salerno. The study aims to enroll 220 adult patients (≥18 years) with a confirmed diagnosis of CHF—classified as heart failure with reduced ejection fraction (HFrEF), heart failure with mildly reduced ejection fraction (HFmrEF), or heart failure with preserved ejection fraction (HFpEF)—and functional class I to III according to the New York Heart Association (NYHA) classification. All participants must be clinically stable and on optimized medical therapy for at least one month prior to enrollment (Figure 1).

Participants will be allocated to the telerehabilitation or standard rehabilitation arm based on patient preference and logistical eligibility (e.g., home safety, access to digital devices, internet connectivity). Although this approach does not involve randomization, both groups will be enrolled under identical inclusion and exclusion criteria. To mitigate potential selection bias, comprehensive baseline characterization and statistical adjustment (e.g., propensity score methods) will be applied. Patients in the intervention group (TELEREHABILITATION-YES) will undergo an 8-week individualized cardiac rehabilitation program performed at home, supported by the Khymeia Virtual Reality Rehabilitation System (VRRS). The program includes real-time video-supervised sessions with a physiotherapist, and continuous monitoring through medical-grade wearable sensors that collect electrocardiogram (ECG), heart rate (HR), peripheral oxygen saturation (SpO_2_), and blood pressure (BP) data. The system also records exercise performance using inertial movement sensors, and all data are transmitted securely to a central digital platform for remote clinical oversight and feedback.

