## 3. Groups and Interventions

Participants enrolled in the study will be allocated to one of two groups based on their voluntary acceptance of the telerehabilitation modality:1.TELEREHABILITATION—YES (Remote Group)2.TELEREHABILITATION—NO (In-Person Group)

Both groups will undergo an 8-week individualized CR program based on international guidelines for heart failure rehabilitation [29]. The intervention includes a combined training protocol delivered 5 times per week for the first 4 weeks, and 3 times per week for the subsequent 4 weeks. Each session lasts approximately 60 min and is structured as follows (Table 2):10 min of interval training (warm-up) including flexibility, breathing, and coordination exercises;40 min of endurance training using a stationary bicycle, aiming at 70% of VO_2_ peak (as determined by baseline CPET) or 75–80% of maximum HR if CPET is not available [30,31,32,33,34];10 min of cool-down exercises with stretching and breathing techniques.

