## 12. Study Limitations and Future Directions

This study has several limitations that should be acknowledged. First, the single-center design may limit the generalizability of findings, as patients are recruited from a single university hospital with specific technological infrastructure and clinical pathways. Future multicenter trials are needed to validate the model in more diverse healthcare settings and populations.

Second, the study does not employ randomized allocation to intervention and control groups, which introduces the potential for selection bias. Although careful matching and baseline characterization are planned to mitigate this issue, a randomized controlled trial would offer a higher level of evidence and should be considered in future research phases. Nevertheless, this pragmatic allocation strategy is particularly relevant in the context of the Salerno province, which includes geographically complex and low-accessibility areas such as the Amalfi Coast and inland Cilento. These regions are often underserved in terms of rehabilitation services. By allowing patients to choose their rehabilitation modality, the protocol increases accessibility and adherence, reflecting the real-world feasibility of implementing home-based telerehabilitation programs in underserved or hard-to-reach populations.

Third, the duration of follow-up (24 weeks), while longer than many previous CTR studies, remains insufficient to evaluate long-term outcomes such as rehospitalizations, cardiovascular events, or mortality. Extended follow-up studies will be necessary to assess the sustained impact and safety of the intervention over time.

Fourth, although the study includes multidimensional clinical and biological assessments, it does not incorporate a formal cost-effectiveness analysis, which is crucial for informing health policy decisions and large-scale implementation. The economic sustainability of the proposed model should be evaluated in subsequent studies.

Fifth, while body weight, height, and BMI are routinely collected and monitored throughout the study, more advanced measures of body composition—such as visceral adiposity—are not included. Considering that fluctuations in body weight are a recognized predictor of heart failure decompensation, this parameter remains clinically relevant and will be carefully analyzed, although the lack of imaging-based adiposity assessment represents a limitation.

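### Section 9.2 fixes an unadjusted chi-square or Fisher test for adverse events although patients choose their arm, so case mix can hide or create a difference in harm

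*Protocol article*

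**What the plan says.** **How the arms are formed.** The Study Design and Population section states: "Participants will be allocated to the telerehabilitation or standard rehabilitation arm based on patient preference and logistical eligibility". Section 3 says allocation is "based on their voluntary acceptance of the telerehabilitation modality".

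**What is promised against selection bias.** The same Methods section says that "comprehensive baseline characterization and statistical adjustment (e.g., propensity score methods) will be applied". The promise is not limited to one endpoint. Section 12 adds: "Although careful matching and baseline characterization are planned to mitigate this issue".

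**What section 9 writes down.** Adjustment appears once, in the logistic regression for the primary responder endpoint in section 9.1: "The model will be adjusted for clinically relevant covariates identified through baseline comparisons using ANOVA or chi-square tests". In section 9.2, repeated secondary outcomes are compared across timepoints by "one-way repeated measures ANOVA for normally distributed data, or Friedman test for non-parametric data", in which time is the only factor. Categorical variables, with the share of patients having adverse events as the example, "will be compared using the Pearson chi-square test", or Fisher's exact test where appropriate. Section 9.2 names no covariate, stratum, weight or matched sample.

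**How the adverse-event outcome is defined.** Section 9.2 works with the share of patients who have an event. Table 3 defines the measure as events divided by treatments administered.

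**The concern.** A Pearson or Fisher test on a two-by-two table estimates an effect of the rehabilitation mode only if the two groups would have had the same event risk under the same care. Self-selected arms give no such assurance. Eligibility covers NYHA I to III and all ejection-fraction classes, so there is ample room for the arms to differ in prognosis.

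Safety is one of the stated aims in the abstract. Section 10 expects real-time monitoring to improve safety, and section 11 would use a low adverse-event rate to support feasibility. If section 9.2 is followed as written, the comparative safety statement rests on a crude contrast while the main efficacy model is adjusted. The two results would not be on the same footing, and a reader could not tell a safety difference from a difference in who chose which arm.

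**Working it through.** **1. Is it a between-arm test?** Section 9.2 does not say what is compared with what. Three things point to the arms. Table 3 has no baseline assessment of adverse events, so there is no before-after contrast. The comparisons across timepoints are given to other tests. Pearson's chi-square and Fisher's exact test are tests for independent groups. This is a strong inference, not stated text.

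**2. Is there a figure in the plan to reproduce?** No. The sample size of 200 (220 with dropout) concerns VO2max. The documents give no adverse-event rate, NYHA split or arm split, so everything below is assumed.

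**3. Crude comparison with no true effect.** Assumed event risk: 30% in NYHA III, 10% otherwise, the same in both arms. For an arm with NYHA III share p:

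crude risk = p × 0.30 + (1 − p) × 0.10

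| NYHA III share, remote / in-person | Crude risk, remote | Crude risk, in-person | Crude ratio |
|---|---|---|---|
| 25% / 45% | 0.075 + 0.075 = 15% | 0.135 + 0.055 = 19% | 0.79 |
| 30% / 40% | 0.09 + 0.07 = 16% | 0.12 + 0.06 = 18% | 0.89 |
| 40% / 30% | 18% | 16% | 1.125 |
| 45% / 25% | 19% | 15% | 1.27 |

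In the first row a true relative increase of 1/0.789 − 1 = 27% in the remote arm would appear as no difference, because 15% × 1.267 = 19%. In the second row a true increase of 12.5% would disappear. In the last row a 27% excess appears where none exists.

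The ratio does not depend on how common events are, only on the assumed threefold risk between strata. With risks of 15% and 5% the first row becomes 7.5% versus 9.5%, again 0.79.

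**4. Crude comparison with a true effect.** Assumed: risks of 10% and 30% in the in-person arm, a true within-stratum odds ratio of 2.0, and 100 patients per arm. Doubling the odds gives remote-arm risks of 0.2222/1.2222 = 18.2% and 0.8571/1.8571 = 46.2%.

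| High-risk share, remote / in-person | Crude risks | Crude odds ratio | Approximate chance that the crude test shows significant harm (0.05 two-sided) |
|---|---|---|---|
| 20% / 60% | 23.8% vs 22.0% | 1.11 | 5% |
| 30% / 50% | 26.6% vs 20.0% | 1.45 | 19% |
| 40% / 40% | 29.4% vs 18.0% | 1.89 | 47% |
| 60% / 20% | 35.0% vs 14.0% | 3.30 | 94% |

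Standardised to the pooled case mix (40% high-risk), the true difference is 29.4% − 18.0% = 11.4 points in every row. The crude difference runs from 1.8 points (first row) to 21 points (last row). The 20% / 60% imbalance is deliberately large.

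**The case against.** **The article may simply be brief.** The adjustment promise in Methods is general and section 12 mentions matching, so a chi-square test on a matched sample is conceivable. Which analyses use such a sample is a detail that an analysis plan could hold. This stands in part: the text does not rule it out. But section 9.2 is not silent. It fixes a test and does not connect it to a matched or weighted sample, and the one adjustment that section 9 describes is by regression covariates.

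**Harm will be hidden.** A reader might infer that fitter, better-supported patients choose telerehabilitation, so that the crude test masks harm. The documents do not support that direction. Sections 11 and 12 describe the remote option as suited to people with limited mobility or transport, or in areas with poor access. That could make the remote arm the sicker one and create a false excess.

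**A propensity score is already in place for the primary endpoint.** A reader might infer this too, but section 9.1 plans covariate adjustment only. Propensity methods appear once, in Methods, as an example.

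**Adjustment would not rescue power.** This stands. With 35% NYHA III overall, an in-person risk of 17% and 100 per arm, a true 27% relative increase (17% versus 21.5%) would be significant only about 13% of the time even with perfect adjustment; for 12.5% it is about 7%. Adjustment removes bias in the estimate. It does not make a small safety signal detectable, and models with many covariates are unstable when events are few.

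**Some asymmetry is beyond adjustment.** Section 8 counts device issues among adverse events, while the in-person arm uses no remote-monitoring devices. This also stands.

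**Conclusion.** The point holds as a gap between the protection that Methods promises and the test that section 9.2 fixes. Followed as written, section 9.2 gives a confounded comparison of adverse events. The bias can go either way, and the documents do not say which arm will be sicker. Its size cannot be derived from them. Under the assumed threefold risk in NYHA III, a 20-point imbalance moves a true ratio of 1 to 0.79 or 1.27, and a 10-point imbalance to 0.89 or 1.125. The conclusion rests on reading the test as between arms, which is strongly implied but not stated, and on no matched sample being intended there. It does not show that harm will be missed, only that the crude test cannot separate harm from case mix. The change is worth making because it needs only baseline data that are already collected.

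**What to change.** - State in section 9.2 that the categorical comparison is between arms, and on which sample it is run.
- Keep the crude adverse-event table, as description only.
- Base the between-arm safety statement on an adjusted risk difference with a confidence interval. Use one prespecified adjustment set, or the propensity score mentioned in Methods as weights or as a single covariate. Use Firth penalisation if events are few.
- Reconcile the outcome. If it is the share of patients with an event (section 9.2), use the adjusted model above. If it is events over treatments administered (Table 3), use a rate model with the number of treatments as offset and report an adjusted rate ratio. If both are wanted, name the main one.
- Report device issues separately, since adjustment cannot make them comparable between arms.

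The cost is analysis wording, with no new visits or data. The adjustment set or score has to be defined, because section 9.1 currently picks covariates from baseline tests. The downside is wider intervals and limited precision when events are few, so the result should be read from the interval and not from a significance test.
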